### Sample size calculation

#### Primary outcome: reduction in pain intensity

With 85 patients in each arm of the trial, there will be 90% power to detect a difference of 0.50 standard deviations in our primary outcome measure of pain. For the Low Back Pain rating scale, and assuming a between-person *SD* of 3.0 [6], a difference of 1.5 units can be detected with 90% power. A clinically significant difference in pain intensity is regarded as being at least 2 units [23].

#### Presence of Modic changes

For the secondary aim of assessing whether the effect of antibiotics compared to placebo is dependent on the presence of Modic changes, the relevant power calculation is that for detecting an interaction between antibiotic intervention and Modic status. We anticipate half the patients will demonstrate Modic changes at baseline, and assuming a between-person SD of 3.0 in LBP rating scale [6], 85 patients per randomised arm will have 80% power to detect an interaction effect of size 2.6, meaning that the effect of antibiotics in patients with Modic changes is 2.6 units higher than in patients without Modic changes. The value of 2.6 was observed in Albert et al. [6], and therefore, there is sufficient power to detect a large antibiotic effect in the Modic changes subgroup compared with little effect, if any, in other patients. If there is a significant interaction effect between antibiotic effect and Modic changes, this will provide evidence to support the hypothesis that infection is important in the underlying pathogenesis in this subgroup of patients with chronic low back pain and disc herniation. All analyses will adjust for the baseline value of the relevant outcome variable, and this will further increase the power by an amount depending on the size of the baseline to follow-up correlation in the outcome.

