## Background

Low back pain is a major global health issue. It is not only the leading cause of disability worldwide [1], but evidence-based treatments are limited and only provide small to moderate benefits [2]. Recently, there has been enormous interest and controversy around a potential new treatment approach involving antibiotic therapy for a specific patient subgroup with chronic low back pain [3, 4]. The approach is based on the hypothesis that some individuals that sustain a disc herniation develop chronic low back pain due to a secondary, low-grade infection that develops in the disc [5]. This infection may result from a breach in the disc’s integrity allowing low virulent organisms that are commonly present on human skin to travel via the blood stream to the disc, resulting in infection, adjacent bone oedema (Modic change) and disabling back pain.

The first randomised controlled trial of antibiotic therapy by Albert et al. showed that amoxicillin-clavulanate (500/125mg) three times per day for 100 days was more effective than placebo for chronic low back pain with disc herniation and adjacent Modic type 1 changes (vertebral bone oedema) [6]. These findings were considered analogous to the discovery of *Helicobacter pylori* and the treatment of gastric ulcers, where a previously common, non-infectious condition was found to have an infective origin. While these results show promise for the prescribing of antibiotics for a specific patient subgroup with low back pain, commentaries in the BMJ highlight the importance of further research before a change in practice can be justified [3, 4]. More recently, a second clinical trial by Bråten et al. found that treatment with antibiotic therapy, amoxicillin (750 mg) 3 × per day for 3 months, did not provide a clinically important benefit in patients with chronic low back pain and Modic type 1 or 2 changes at the level of a previous disc herniation [7]. While these trials by Albert et al. and Bråten et al. provide contrasting results regarding the efficacy of antibiotic treatment for chronic low back pain, there are key differences in their methodology, including differences in the type of Modic changes examined and the type of antibiotic treatment prescribed, which may explain the disparity [6, 7].

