## Discussion

We present the protocol for a double-blind, randomised, placebo-controlled trial investigating whether antibiotic treatment (amoxicillin-clavulanate) is effective in the management of chronic low back pain with disc herniation and if the presence of Modic changes predicts those individuals more likely to respond to antibiotic therapy. If antibiotic treatment is found to be effective, it will provide high-quality evidence to support this therapeutic approach for a targeted patient subgroup with chronic low back pain and disc herniation. However, if it is not effective, it will provide important data to prevent the inappropriate use of antibiotics in this patient population.

The current trial was designed to examine the efficacy of antibiotic treatment for low back pain with disc herniation, in conjunction with considering the study methodology and results of previous clinical trials. The clinical trials of Albert et al. [6] and Bråten et al. [7] differ in several ways in their methodologies (Table 2). With respect to the choice of antibiotic treatment, Albert et al. investigated the efficacy of the antibiotic, amoxicillin-clavulanate [6], based on the results of a previous biopsy study which found several different types of bacteria to be present in the spinal discs of people with low back pain [24], as well as evidence that the amoxicillin-clavulanate can enter the lumbar disc [13]. In contrast, the trial by Bråten et al. examined the efficacy of the antibiotic, amoxicillin [7]. Amoxicillin-clavulanate is not available in Norway where the study was undertaken. The investigators suggest that the use of amoxicillin with clavulanic acid may increase the risk of side effects and may not be required as culture studies in Europe indicate little or no resistance to *Cutibacterium acnes* [25].

**Table 2 Tab2:** Comparison of clinical trial methodologies

Clinical trials/protocol	Albert et al. [6]	Bråten et al. [7]	[name] et al. (2021)
Patient subgroup			
	Participants with disc herniation and type 1 Modic changes	Participants with disc herniation and type 1 and 2 Modic changes	Participants with disc herniation—with and without type 1 and 2 Modic changes
Intervention			
	Amoxicillin-clavulanate (500/125 mg) 100 days	Amoxicillin (750 mg) 3 months	Amoxicillin-clavulanate (500/125 mg) 3 months
Other treatments allowed			

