There has been variation between the clinical trials in the additional care participants are allowed to access. While participants in the Albert et al. trial were not allowed to seek other treatments during the 1-year trial period [6], those in the Bråten et al. trial were permitted to continue ongoing treatment, but recommended not to start additional treatments or use non-steroidal anti-inflammatory drugs [7]. We have chosen to allow participants in both groups to seek usual care, including the use of analgesia and non-steroid anti-inflammatory medication. We do not expect usual care to affect the proposed mechanism of the antibiotic therapy that is being tested in this trial and usual care to be balanced across the treatment groups due to randomisation. All care provided to each individual patient in both groups will be documented.

The previous clinical trials of antibiotics both targeted patient subgroups with disc herniation and Modic changes, but with Albert et al. recruiting patients with type 1 Modic changes only [6] and Bråten et al. including those with type 1 or 2 Modic changes [7]. It is hypothesised that Modic changes result from a bacterial infection in the disc with cytokine and propionic acid production causing inflammation in the adjacent bone. While a biopsy study by Albert et al. has shown that 80% of individuals with infected disc material developed new Modic changes [24], it is unclear whether Modic changes are important in patient selection. In the biopsy study, low virulent bacteria were also identified in participants who did not develop new Modic changes, and conversely, those that had no bacteria present also developed Modic changes [24]. Moreover, our systematic review found that disc herniation was the most common diagnosis in those individuals with back pain and bacterial infection, and there was a relationship between the presence of bacteria and low back pain with disc herniation [8]. Based on these results, our trial will examine the efficacy of antibiotic treatment in individuals with chronic low back pain and disc herniation confirmed on MRI. There is a potential with restricting our criteria to those with Modic changes that we could miss a subgroup of patients that may benefit from antibiotics. However, to determine the role of Modic changes, we will include people with and without Modic changes and determine whether the presence of Modic changes predicts those individuals more likely to respond to antibiotic treatment.

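### The 2.6-unit interaction behind the 80% power comes from a trial with no patients lacking Modic changes, so the claim that power is sufficient does not follow

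*Protocol article*

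**What the plan says.** Under Presence of Modic changes (Sample size calculation), the protocol sizes the test of interaction between treatment arm and baseline Modic status. The inputs are "We anticipate half the patients will demonstrate Modic changes at baseline" and "assuming a between-person SD of 3.0 in LBP rating scale", and the result is that "85 patients per randomised arm will have 80% power to detect an interaction effect of size 2.6". The interaction is defined as a difference between two treatment effects: "the effect of antibiotics in patients with Modic changes is 2.6 units higher than in patients without Modic changes".

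The next sentence attributes 2.6 to the first antibiotic trial. From that it concludes that power suffices to distinguish a large effect in the Modic subgroup from little or no effect in the others.

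The Discussion describes the same source trial as "recruiting patients with type 1 Modic changes only"; the Background and Table 2 agree. Table 2 describes the present population as having disc herniation "with and without type 1 and 2 Modic changes".

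**The concern.** An interaction with Modic status can be observed only in a trial that has patients on both sides of the comparison. The source trial had one side only. Its 2.6 therefore cannot be the quantity the protocol defines, and the step from that trial to sufficient power here has a gap.

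For 2.6 to carry over, two conditions must hold:

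- patients without Modic changes gain nothing from the antibiotic;
- the full type 1 effect holds in a Modic group that pools types 1 and 2.

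The protocol's own rationale secures neither. The Background leaves open whether everyone with disc herniation might respond, and the Discussion gives that possibility as the reason for not restricting entry to Modic patients. The Background also reports that the second trial, in types 1 or 2 and with a different antibiotic, found no clinically important benefit.

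The Modic question is a named aim and sets this trial apart from the two earlier ones. If its power is taken to be 80% without conditions, a null interaction may be given more weight than the design can support.

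**Working it through.** **Inputs.** 85 patients per arm, half with Modic changes (42.5 per cell), SD 3.0 and interaction 2.6, all from the Sample size calculation section. That section does not state the significance level; two-sided 0.05 is assumed. The baseline to follow-up correlation r is not given either, so r = 0 is used to reproduce the stated figure and r = 0.3 and 0.5 as an assumed range.

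**Reproducing the stated power.**

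- SE of the interaction = 3.0 × √(4/42.5) = 0.920.
- Power = Φ(2.6/0.920 − 1.960) = 80.6%. With the noncentral t on 166 degrees of freedom it is 80.2%.
- One-sided 0.05 would give 88.1%, so two-sided 0.05 is the reading that fits.

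**Margin.** The smallest interaction with 80% power is (1.960 + 0.842) × 0.920 = 2.58 unadjusted. Baseline adjustment multiplies the SE by √(1 − r²):

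- r = 0.3: SE 0.878, smallest interaction 2.802 × 0.878 = 2.46.
- r = 0.5: SE 0.797, smallest interaction 2.802 × 0.797 = 2.23.

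**What 2.6 implies for this trial.** The interaction equals the effect with Modic changes minus the effect without. With 2.6 taken as the effect in Modic patients, the no-Modic effects below are illustrative assumptions:

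| Effect without Modic changes | Interaction | Power, unadjusted | r = 0.3 | r = 0.5 |
|---|---|---|---|---|
| 0 | 2.6 | 81% | 84% | 90% |
| 0.4 | 2.2 | 67% | 71% | 79% |
| 1.0 | 1.6 | 41% | 45% | 52% |

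The same rows apply if the no-Modic effect is zero but the effect in the pooled type 1 and 2 group is 2.6, 2.2 or 1.6.

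**Precision.** The unadjusted 95% confidence interval for the interaction is the estimate ± 1.960 × 0.920 = ± 1.80. An estimate of 1.0 would be non-significant, with an interval from −0.8 to 2.8 that still contains 2.6.

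**The case against.** The strongest reply is that the protocol largely discloses its scenario. The power sentence is correct as written. The next sentence says that the value 2.6 was seen, not in so many words that an interaction was, and it contrasts a large effect with little or none. In the zero case 80% holds. Planned baseline adjustment then adds power, as the same section says. All of this stands, and it limits the point to the source of 2.6 and the conclusion drawn from it. It does not remove the point: a little effect is not zero, there is almost no unadjusted margin, and adjustment at r = 0.5 would absorb a no-Modic effect of only about 0.37 (2.6 − 2.23).

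Several stronger readings are tempting, but the document does not support them:

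- *A calculation error.* There is none; the 80% reproduces.
- *The test will more likely miss than detect.* Unadjusted power falls below 50% only for interactions under 1.80. At 2.2 it is 67%, and nothing in the protocol fixes the true value.
- *The two power statements conflict*, because 2.6 in half and 0 in half average 1.3, below the 1.5 used for the main comparison. They are detectable differences for separate questions and need not share one scenario.
- *The different regimen in the source trial undermines 2.6.* The document gives no quantitative link between regimen and interaction.
- *A type 1 contrast is required.* That is a preference; the stated aim concerns the presence of Modic changes.
- *The protocol plans to treat a null interaction as evidence of no moderation.* It says only what a significant interaction would mean.

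**Conclusion.** The point holds as a fault of source and inference. The value 2.6 cannot be an observed interaction with Modic status, because the protocol describes its source as having no patients without Modic changes. The document does not say what kind of quantity 2.6 was there; at most it is a treatment effect within type 1 patients.

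The 80% is therefore conditional on a zero effect without Modic changes and on the full 2.6 in a pooled type 1 and 2 group. Within the range shown, departures from those conditions take unadjusted power from 81% to between 67% and 41%, and adjusted power to between 79% and 45%. These figures rest on two-sided 0.05, SD 3.0, equal cells, complete data and the assumed correlations. The aim is secondary, and neither the primary sample size nor the primary analysis is affected.

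**What to change.** Revise the Presence of Modic changes paragraph as follows:

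1. State that 2.6 is taken from a trial confined to type 1 Modic changes with no non-Modic group, and that the 80% assumes no effect without Modic changes and the full 2.6 in the pooled type 1 and 2 group.
2. Replace the conclusion that power is sufficient with a conditional statement giving power for interactions of 2.6, 2.2 and 1.6: 81%, 67% and 41% unadjusted, and about 84–90%, 71–79% and 45–52% after baseline adjustment at an assumed correlation of 0.3 to 0.5.
3. Commit to reporting the interaction with its 95% confidence interval, and say that a non-significant result will not be taken as evidence that Modic status does not matter.

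The cost is wording and a less favourable stated power. Trial status reports that randomisation is finished, so the change concerns how the result is framed and interpreted, not recruitment.

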### Statistical analysis

Summary statistics comparing randomised arms at baseline will be tabulated. Intention-to-treat analyses of primary and secondary continuous outcomes will be performed by linear regression adjusting for the baseline of the outcome variable. Logistic regression will be performed for binary outcomes. Adjustment for imbalanced baseline factors, including the presence of symptoms other than low back pain, will be performed as supplementary analyses. We will perform a per-protocol analysis as a secondary analysis, defining compliance to the protocol as taking ≥ 80% of the planned number of pills, which is consistent with methodology from a previous trial [7]. Analysis of the moderating effect of Modic change status will use regression models with an interaction term between intervention arm and Modic change status, and adjusting for baseline values of the outcome variables. Missing outcome data for all analyses will be imputed via multiple imputation methods using relevant baseline and post-baseline measurements.

### Economic analysis

An economic evaluation will be performed in conjunction with the clinical trial to investigate the cost-effectiveness and cost-utility of amoxicillin-clavulanate compared with placebo. The economic evaluation will be conducted from a societal and health care perspective and all relevant costs will be included. Costs of the antibiotic treatment will be included, along with costs of other health care utilisation, such as other prescription medication, care by general practitioners, allied health professionals and medical specialists, hospitalisation and professional home-care. Costs for patients and their family will also be measured. Finally, costs of productivity loss due to paid and unpaid work will also be included. Pain will be primary outcome measures in the cost-effectiveness analysis. For the cost-utility analysis, utilities will be expressed as quality-adjusted life years (QALYs) as measured using the EQ-5D-5L.

The mean differences and 95% confidence intervals for total costs, costs of health care utilisation and costs of productivity loss between the antibiotic and placebo groups will be obtained by bias-corrected and accelerated bootstrapping using 5000 replications. Cost-effectiveness ratios will be estimated by dividing the difference in the total costs between the antibiotic group and the placebo group by the difference in the mean effects for pain intensity and disability. A cost-utility ratio will be determined for QALYs gained over a 12-month follow-up. To determine these ratios and uncertainty surrounding the ratios, the bias-corrected percentile bootstrapping method (5000 replications) will be applied and will be graphically presented on cost-effectiveness planes. Acceptability curves will also be used to determine the probability that the antibiotic therapy was cost-effective compared with placebo at different values of the maximum acceptable ratio.

### Data integrity and management

All collected data will be recorded using case report forms or questionnaires and stored in a locked area in the Department of Epidemiology and Preventive Medicine at Monash University with secured and restricted access. The electronic data will be stored in a password-protected database with secured and restricted access. All data collected will be kept strictly confidential. Data transfer will be encrypted with all data de-identified. Only research personnel on the project will have access to the study data. The trial will be audited through the Monash University School of Public Health and Preventive Medicine and the Alfred Hospital Human Research Ethics Committee.

### Withdrawal

If participants withdraw before completion of the study, the reason and date will be recorded and participants will be asked if they can complete the remaining outcome measures.

### Monitoring

The principal investigators will monitor the conduct and progress of the project and ensure that all trial procedures are compliant with the trial protocol. The research team will have regular meetings to ensure efficient study execution and ongoing monitoring of adverse events. Any changes in the study protocol or procedures will be first approved by the Alfred Hospital Human Research Ethics Committee. Deviations from the original protocol will be fully documented using a breach report form and the protocol will be updated on the Australian New Zealand Clinical Trials Registry. The trial will be formally stopped if metformin is found to have unacceptable side effects.

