**Methods:**

One hundred and seventy individuals with chronic low back pain will be recruited through hospital and private medical and allied health clinics; advertising in national, community and social media; and posting of flyers in community locations. They will be randomly allocated to receive either amoxicillin-clavulanate (500 mg/125 mg) twice per day for 90 days or placebo. The primary outcome measure of pain intensity will be assessed using the Low Back Pain Rating scale and a 100-mm visual analogue scale at 12 months. Secondary measures of self-reported low back disability and work absence and hindrance will also be examined, and an economic analysis will be conducted. Intention-to-treat analyses will be performed.

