### Intervention

Participants in the intervention arm will receive the antibiotic, amoxicillin-clavulanate (coamoxiclav; 500 mg/125 mg) tablets (Aspen Pharmacare Australia, NSW), two times per day for 90 days, and those in the control group will receive microcrystalline cellulose tablets, which will be identical in size, colour, coating and packaging to the active tablets. We selected amoxicillin-clavulanate for several reasons: (i) it is widely used in clinical practice; (ii) the initial clinical trial by Albert et al. found amoxicillin-clavulanate to have a beneficial effect on chronic low back pain with disc herniation and Modic changes type 1 [6]; (iii) our systematic review of biopsy studies showed that a variety of bacteria are present in the spinal disc and a broad-spectrum antibiotic, such as amoxicillin-clavulanate, is needed [8]; and (iv) there is evidence that it can penetrate the spinal discs [13]. All participants will be provided with usual care by their treating health practitioners.

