**Table 1 Tab1:**
[figure not shown]
Schedule of enrolment, interventions and assessments

*Adverse events were assessed with a blood test at additional time points not presented in this table; including 2 and 6 weeks to monitor liver function and any other adverse events

Eligible participants will be randomised, asked to complete the baseline questionnaire and sent the first 3 months of amoxicillin-clavulanate or placebo, followed by the second 3 months half way through the trial. A blood test will be performed at 2, 6 and 12 weeks to monitor liver function and any other adverse events. Participants will also be requested to report any adverse events to the research staff spontaneously. Details of major adverse events and their relationship with study intervention will be recorded and reported to the ethics committees. If participants experience adverse events as a result of this research project, appropriate medical treatment will be provided to participants. All participants’ physician will be notified of their inclusion in the trial.

Participants will be contacted at 3, 6, 9 and 12 months to continue to monitor any side effects of the treatment and collect outcome data. A lumbar spine MRI will be conducted at 12 months to assess the presence of Modic changes. The same researchers, who are blinded to treatment allocation, will measure all clinical variables, administer questionnaires, monitor compliance and record adverse events. Unblinding will be allowed under certain circumstances, such as a participant’s doctor requiring their allocated intervention to ensure they receive the appropriate medical care. Compliance by trial medication will be assessed by pill count. Participants will not be paid for their participation in the trial, but they will be reimbursed for parking and transport costs.

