## Trial status

The study protocol version number and date is version 4 16 March 2018. Recruitment began on 14 September 2015, and we have randomised 166 participants to date. We randomised all participants by 27 May 2021, and the 12-month outcomes will be completed by 27 May 2022.

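### The article's only trial stopping rule names metformin, a drug given in neither arm, instead of amoxicillin-clavulanate

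*Protocol article*

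**What the plan says.** The last sentence of Methods, Monitoring in the protocol article reads: "The trial will be formally stopped if metformin is found to have unacceptable side effects".

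The treatments are set out in Methods, Intervention. For the active arm: "Participants in the intervention arm will receive the antibiotic, amoxicillin-clavulanate (coamoxiclav; 500 mg/125 mg) tablets". For the comparator: "those in the control group will receive microcrystalline cellulose tablets". The Abstract agrees: "They will be randomly allocated to receive either amoxicillin-clavulanate (500 mg/125 mg) twice per day for 90 days or placebo".

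Other safety provisions are spread over several sections. Study procedure and Adverse events provide for blood tests at 2, 6 and 12 weeks. Study procedure adds: "Details of major adverse events and their relationship with study intervention will be recorded and reported to the ethics committees". Monitoring itself has the research team meeting regularly to follow adverse events.

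**The concern.** A stopping rule has to name the exposure whose harms would trigger it. This one names a drug that no participant receives as study treatment. Taken at its word, it places no condition on amoxicillin-clavulanate, whatever that drug's side effects turn out to be.

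The rule protects participants. The Discussion names liver injury as a possible side effect of the study drug, while calling the risk extremely low, and treats adverse events as an important consideration over a 3-month course. A reader who wants to know when the trial would be halted for such harm finds only this sentence.

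**Working it through.** The check is mainly textual.

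**1. Is metformin a study treatment, or mentioned anywhere else?**

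| Place in the article | Drug named |
|---|---|
| Abstract, Methods | amoxicillin-clavulanate or placebo |
| Methods, Intervention | amoxicillin-clavulanate 500 mg/125 mg twice daily for 90 days, or microcrystalline cellulose |
| Methods, Exclusion criteria | no mention of metformin |
| Methods, Concomitant medication use | non-opioid analgesics and non-steroidal anti-inflammatory drugs |
| Discussion | amoxicillin-clavulanate, and amoxicillin in an earlier trial |
| Methods, Monitoring | metformin |

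Metformin appears once, in the stopping sentence. It is neither a treatment, a comparator, an excluded drug nor a listed co-medication.

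**2. Does another sentence supply the correct rule?** The remaining safety text covers scheduled blood tests, recording and reporting of adverse events, medical treatment of those affected, and unblinding for medical care (Study procedure; Adverse events); withdrawal of individual participants (Withdrawal); audit (Data integrity and management); and team meetings (Monitoring). None of these gives a condition for stopping the trial, so nothing else in the article fills the gap.

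**3. Could the text be superseded or damaged?** The sentence is current Methods text, not an amendment log. It is complete and grammatical, with no sign of redaction or faulty extraction.

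**4. Does it affect the statistical design?** No. The plan's own figure reproduces. With 85 per arm, a difference of 1.5 units, SD 3.0 (0.50 SD) and two-sided alpha 0.05 (assumed, as the article does not state it), power is 90.3%. The number needed for 90% power is 85 per arm. Neither depends on the stopping sentence.

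**5. How much dosing remained at the end of randomisation?** This describes the remaining exposure; it does not measure the error. From Trial status, recruitment began on 14 September 2015 and "We randomised all participants by 27 May 2021".

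- Interval: 14 September 2015 to 27 May 2021 = 2,082 days.
- Last possible end of a 90-day course: 27 May 2021 + 90 days = 25 August 2021.
- Share still within a 90-day course at close, assuming even accrual: 90 / 2,082 = 4.3%.
- Number, using the 166 reported as randomised to date: 166 × 90 / 2,082 = 7.2.
- If the closing accrual rate was half to double the average: 3.6 to 14.4.

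These counts cover both arms. With equal allocation about half, 7.2 / 2 = 3.6, would be on amoxicillin-clavulanate. The accrual pattern is not given, and the target was 170, so these are rough figures.

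**The case against.** The strongest reply is that this is an obvious slip with no consequence. The trial has one active drug, named throughout, and nobody reading Monitoring could substitute anything else. Safety oversight does not hang on this word: blood tests, assessment of whether events are related to the study drug, reports to the ethics committees, unblinding for care, and audit all concern the treatment given. On that view it is an editorial correction only. The approved protocol, version 4, is also not shown and may be right.

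Much of this stands. The intended meaning is plain, the practical risk is limited, and nothing shows that conduct or participant safety was affected. The error may exist only in the article. What the reply does not remove is that the sentence is an operative safety rule, the only one of its kind in the article, and wrong as written. The other provisions limit the consequence, but none of them is a stopping condition. It is also fair to say that the accrual arithmetic gives the error no extra weight: it shows only that little dosing was left when randomisation closed.

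**Conclusion.** The concern holds. The article's single trial-level stopping statement names a drug that is in neither arm, so as written it is not tied to side effects of amoxicillin-clavulanate. The size of the error is one word in one sentence. It should be fixed because it sits in a safety rule, but it is not a threat to the trial: power, efficacy analysis and routine safety monitoring are unaffected.

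The conclusion rests on the article alone. That amoxicillin-clavulanate was meant is an inference, though a safe one. How the word came to be there is unknown, and version 4 may have the correct drug or further stopping criteria. The lack of a numerical threshold for what counts as unacceptable is not part of this point, since the full protocol may supply it.

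**What to change.** In Methods, Monitoring, replace *metformin* with *amoxicillin-clavulanate*. Compare the sentence with the ethics-approved protocol version 4. If that document has the same wording, correct it through the ethics committee, by the route Monitoring already sets for protocol changes.

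The same comparison can settle a separate wording problem. Study procedure describes tablets being sent for a first 3 months, "followed by the second 3 months half way through the trial", which does not fit a 90-day course. No common origin with the metformin error is claimed.

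The cost is a one-word correction to the article, plus a submission to the ethics committee only if version 4 carries the error. No analysis or sample size changes.
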